### 2.7. Intervention Implementation

Once randomization is complete, participants will receive printed and verbal standardized instructions to maintain their usual lifestyle habits throughout the study period, except for nut consumption, where the following group-specific instructions will be provided:Control group (CG): Participants will be instructed to continue their habitual diet while avoiding direct nut consumption, although the sporadic consumption of foods that may contain trace amounts of nuts as ingredients (e.g., baked goods, ice cream) does not constitute a protocol violation.Intervention groups (IG-30 and IG-60): Participants will be instructed to consume 30 g or 60 g of unsalted, unroasted mixed nuts daily and to exclusively consume the amount of nuts provided by the researchers, refraining from consuming other sources of nuts. For the participants in the CG, sporadic exposure to trace amounts of nuts in processed foods (e.g., baked goods, ice cream) will be acceptable.

The nuts (a mixture of almonds, walnuts, pistachios, and hazelnuts) will be provided free of charge, in daily portions, to participants in the intervention groups for the full duration of the trial. The participants will be asked to incorporate nuts into their usual diet and to consume them in any uncooked manner they prefer, such as alone (only nuts), with salad, or yogurt.

At months 2 and 4, participants will be instructed to collect the prepacked bags containing the daily portions of nuts required for each intervention group during the subsequent period (i.e., participants in IG-30 will receive 30 g bags, and those in IG-60 will receive 60 g bags). To maintain a single-blind design, the nuts will be provided in person for each participant by a researcher who is not involved in clinical assessments. The bags containing the daily content of nuts will be specifically produced for the trial in accordance with established quality standards and sealed under a protective atmosphere. Each bag will contain a fixed mixture of nuts in the following proportions: 35% almond, 35% walnut, 20% unshelled pistachios, and 10% hazelnut. These nut mix proportions are based on the most consumed nut types in Spain and were designed to provide a balanced profile of fatty acids, micronutrients, and bioactive compounds while reflecting habitual intake, improving palatability and adherence, and facilitating translation into practical dietary recommendations.

### 2.8. Trial Monitoring

Every two weeks, all participants will receive a telephone message via WhatsApp from a member of the research team to reinforce adherence and monitor any adverse effects potentially associated with the intervention. If a participant experiences a suspected allergic reaction, intolerance, or digestive discomfort, the intervention will be immediately and permanently discontinued, and medical evaluation will be recommended.

Intervention compliance will be assessed according to the participants’ report of the consumption of at least 80% of the nut doses provided [61]. In addition, to provide an objective measure of adherence to the nut consumption protocol, blood concentrations of vitamin E (α-tocopherol) will be assessed in the four evaluations. Although the expected magnitude of increase in vitamin E associated with nut consumption varies by nut type, dose, and baseline levels, the available evidence has shown a 5 to 15% increase in plasma α-tocopherol with regular consumption of 30–80 g nuts/day over several weeks to month [62].

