The intention-to-treat (ITT) analysis will serve as the primary analysis to preserve randomization benefits and provide a conservative estimate of treatment effects, whereas the per-protocol (PP) analysis will serve as a sensitivity analysis to assess efficacy under optimal adherence conditions. The ITT analysis will include all randomized participants in their assigned groups regardless of adherence, with missing data handled using multiple imputation or mixed-effects models that accommodate incomplete observations. The PP analysis will include only participants who completed the intervention according to protocol specifications, with adherence thresholds defined a priori (e.g., self-reported consumption of at least 80% of nut doses assigned, and 5–15% increased blood concentrations of α-tocopherol) [61].

The interpretation of clinical significance will be based on established minimal clinically important differences (MCID) for each outcome measure. For example, for the BDI-II, we will apply a 17.5% reduction as determined by Button et al. (2015) [100], who found that this represents the threshold at which patients report feeling “better” based on anchor-based methods. We will also evaluate whether participants transition between established severity categories (minimal: 0–13; mild: 14–19; moderate: 20–28; severe: 29–63) [63]. For the GAD-7, we will use the 4-point MCID threshold established by Toussaint et al. (2020) [101] to assess whether participants cross the clinical cut-off of ≥10 points, indicating clinically significant anxiety [66]. Given the lack of consensus on the MCID for the PSS-10, we will interpret effect sizes of Cohen’s d ≥ 0.5 as clinically relevant [57] and contextualize changes using reference values for the target population [102]. We recognize that in preventive nutritional interventions targeting non-clinical populations, small but consistent effects may have beneficial public health impacts [103], particularly given that dietary modifications represent accessible and low-risk interventions.

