The results will be considered statistically significant at the α = 0.05 level. In the presence of statistically significant effects, post hoc analyses will be conducted using a pairwise comparison test to delineate specific contrasts between each intervention group and the control arm. Furthermore, statistical and clinical significance will be distinguished in our discussion, considering both the magnitude of effects and their potential implications for guidelines recommending nut consumption as a strategy to prevent or improve mental health outcomes. Therefore, when the estimators of associations do not reach statistical significance due to the small difference between the intervention and control groups, the results will be presented for their descriptive value and to inform future RCTs exploring the relationship between nuts and mental health. Although *p*-values are relevant, changes that are not statistically significant can still be clinically meaningful [104].

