### 2.12. Limitations and Contingency Plan

#### 2.12.1. Limitations

The study uses a single-blind design because participants cannot be blinded to nut consumption. This may introduce expectancy bias, but it is mitigated by blinding outcome researchers. Primary mental health outcomes rely on self-report questionnaires and are therefore subject to reporting biases. However, validated instruments and complementary objective measures, such as cognitive tests and biomarkers, are included. Adherence cannot be directly observed in free-living conditions. Monitoring through biweekly contact and determination of vitamin E blood concentrations at each visit improves, but does not guarantee, compliance and does not prevent contamination of the control group. The sample consists of university students aged 18–24 years from a single campus. This limits generalizability but enhances internal validity in an understudied population. The study may be underpowered for small effects, secondary outcomes, or subgroup analyses, particularly if dropout exceeds the anticipated 20%. Finally, the 6-month intervention and follow-up period may be insufficient to assess long-term or delayed effects.

The extensive assessment protocol may increase participant burden and the risk of attrition. Although a validated FFQ will be used, dietary assessment remains imprecise and is subject to underreporting and recall bias. Additionally, some control group participants may live with participants from other study groups, which makes complete prevention of contamination unrealistic. While the CG will be instructed to avoid nuts from any source and the IG-30 and IG-60 groups will be instructed to avoid nuts from non-study sources, accidental or intentional nut consumption may still occur.

Finally, academic stressors (e.g., exams, tight assignment deadlines) and seasonal variations may affect mental health and thereby influence the study associations.

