#### 2.12.2. Contingency Plan

Recruitment and retention: If enrollment targets are not met, recruitment efforts will expand across the university. These efforts will use multiple communication channels, classroom presentations, and student organizations. If necessary, eligibility criteria may be slightly adjusted with ethical approval. If the number of students who drop out exceeds expectations, retention strategies will be intensified. These strategies include increased contact, flexible scheduling, reminders, small incentives, and feedback on selected results. Participants who are unable to continue in person will be encouraged to complete all self-reported assessments remotely to support intention-to-treat analyses.Intervention delivery: A backup nut supply and alternative suppliers will be maintained. Any adverse reactions will lead to immediate discontinuation and medical referral. Participants for whom poor adherence is detected during the intervention will receive individualized support and encouragement to remain in the study, regardless of their level of adherence.Data collection and analysis: Backup equipment and rescheduling windows will address equipment failure, technician strikes, and other unpredictable circumstances. Missing data, except for covariates, will be handled using multiple imputation and mixed-effects models. Sensitivity analyses will be performed to assess potential bias.External and ethical considerations: In the event of public health emergencies, such as the COVID-19 pandemic that emerged in 2020, assessments will shift to remote formats where feasible. Seasonal and academic calendar effects will be addressed analytically. Any protocol amendments will receive prior ethical approval, and robust procedures are in place to manage data security incidents.Monitoring and quality assurance: Study progress, adherence, retention, and data quality will be monitored monthly by the study coordinator and reviewed quarterly by the principal investigator. Serious adverse events or unexpected issues will prompt immediate review and, if needed, consultation with the ethics committee. Vitamin E (α-tocopherol) levels will be measured in all participants at baseline, 3 months, and 6 months, along with dietary intake assessments. Unauthorized nut consumption in the control group will be detected through either increases in vitamin E levels > 5% from baseline or self-reported nut intake in dietary recalls.Academic stressors and seasonal variations: The following strategies will be adopted to address confounding by academic-related stressors (e.g., examination periods, high academic demands) and seasonal factors: (1) randomization, to balance exposure to stressful periods across groups; (2) tracking assessment dates, to categorize examination periods and seasons; (3) repeated-measures mixed-effects models, adjusting for these factors as covariates; and (4) sensitivity analyses, to test the robustness of findings. Furthermore, stress is directly monitored as a primary outcome using the PSS-10 scale and may reflect partially academic-related stress symptoms.

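### Section 2.8 frames routine adverse-effect monitoring by suspected link to the intervention, so unblinded controls who receive no nuts are likely to have minor complaints under-recorded relative to the nut arms

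*Protocol article*

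**What the plan says.** Section 2.8 (Trial Monitoring) sets the contact schedule: "Every two weeks, all participants will receive a telephone message via WhatsApp from a member of the research team". The message has two purposes, to reinforce adherence and to "monitor any adverse effects potentially associated with the intervention". The section then names the events it has in mind and their consequence: "If a participant experiences a suspected allergic reaction, intolerance, or digestive discomfort, the intervention will be immediately and permanently discontinued".

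Other sections give the context:

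- **Control arm (2.7):** controls get no study product. "Participants will be instructed to continue their habitual diet while avoiding direct nut consumption". Sporadic trace exposure through processed foods is tolerated.
- **Blinding (2.6 and 2.12.1):** participants are told their arm straight after randomisation, and "participants cannot be blinded to nut consumption".
- **Serious events (2.12.2):** "Serious adverse events or unexpected issues will prompt immediate review and, if needed, consultation with the ethics committee". This sentence has no limit by arm or by suspected cause.
- **Visit assessments (2.10):** depressive symptoms (BDI-II), anxiety (GAD-7) and sleep (PSQI) are measured in every arm. Table 1 lists no adverse-event variable.
- **Interpretation (2.11):** the article remarks that "dietary modifications represent accessible and low-risk interventions" and intends to discuss "potential implications for guidelines recommending nut consumption as a strategy to prevent or improve mental health outcomes".

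**The concern.** Contacting every arm equally often does not mean ascertaining events equally. The stated scope of the monitoring contains a causal judgement, namely potential association with the intervention. A student eating 30 g or 60 g of nuts a day can readily connect bloating or stomach discomfort with the nuts. A control with the same symptom has little reason to connect it with an instruction to avoid nuts. The consequence attached to the named events, stopping the intervention, also has no counterpart for someone who receives no product.

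Relatedness therefore enters when the event is collected, and it is shaped by knowledge of the arm. In a randomised trial the background rate of ordinary complaints is best removed by comparing arms. That works only if complaints are captured in the same way in each arm.

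What is at stake is the credibility of any statement about minor harms at either dose. An article that may comment on guidelines for nut consumption would be expected to set tolerability beside benefit. With unequal capture, a higher recorded rate in the nut arms could reflect the nuts, the wording of the monitoring, or both, and the data could not tell these apart.

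**Working it through.** **Step 1. Does the stated scope depend on the arm?** The concern rests on wording, and the article gives no adverse-event rate to reproduce, so the sections are set side by side.

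| Feature | Nut arms | Control arm | Source |
|---|---|---|---|
| Fortnightly message | yes | yes | 2.8 |
| Study product to which a symptom could be attributed | 30 g or 60 g daily | none | 2.7 |
| Participant knows the arm | yes | yes | 2.6, 2.12.1 |
| Consequence of a named symptom | intervention stopped | nothing to stop | 2.8 |
| Serious or unexpected events reviewed | yes | yes | 2.12.2 |
| BDI-II, GAD-7 and PSQI at visits | yes | yes | 2.10 |

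The arms differ only in the second and fourth rows, and both bear on non-serious, symptom-type complaints. The concern is therefore confined to those.

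**Step 2. How much could unequal capture matter?**

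Inputs from the protocol:

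- Section 2.4 gives 42 per group before dropout and 20% dropout: 42 / (1 − 0.20) = 52.5, rounded up to 53. This matches the article's own figure.
- Pooled nut arms: 2 × 53 = 106. Control: 53. Total: 3 × 53 = 159, again as stated.

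Assumptions, none of them in the protocol:

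- The true complaint rate *p* is the same in all arms, so the nuts have no effect: 20%, with a range of 10% to 30%.
- All complaints in the nut arms are recorded. A fraction *r* is recorded in controls: 1 (equal), 0.5 (half) or 0 (none).

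Model: recorded nut complaints follow Binomial(106, *p*) and recorded control complaints follow Binomial(53, *p* × *r*). The result is the probability, summed over all pairs of counts, that a two-sided Fisher exact test has a p-value of 0.05 or less.

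Expected counts at *p* = 0.20:

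- nut arms: 106 × 0.20 = 21.2
- controls: 53 × 0.20 × *r* = 10.6, 5.3 or 0

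| Assumed true rate, all arms | Equal capture | Half capture in controls | No capture in controls |
|---|---|---|---|
| 10% | 3.3% | 11.5% | 74.4% |
| 20% | 3.8% | 31.1% | about 100% |
| 30% | 4.0% | 51.7% | about 100% |

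The first column is the ordinary false-positive rate of the test, in either direction. The other two columns show what unequal recording adds.

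**Step 3. Sensitivity to arm size.** The abstract gives 135 participants, which is 135 / 3 = 45 per arm. At a 20% rate the expected counts become 90 × 0.20 = 18 in the nut arms and, with equal capture, 45 × 0.20 = 9 in controls. The same formula with half capture in controls gives about 27% instead of 31%. The conclusion does not turn on which total is right.

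**The case against.** The strongest reply is that the article states no exclusion. All participants are messaged, the wording of the message is not given, and nothing says that a control's report would be discarded or who judges relatedness. The named events are mostly symptoms, which controls can report, and controls may have trace nut exposure. All of this stands. A reader might infer that only intervention-related effects are collected, that controls cannot qualify, and that the recorded control rate is zero by definition. The documents do not support that. They support a likely shortfall in controls of unknown size.

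A second reply is that safety information comes from other sources too. This also stands. A reader might infer that worsening mood or sleep goes unrecorded, or that the control arm is useless for safety. Neither follows: BDI-II, GAD-7 and PSQI are administered in every arm, and section 2.12.2 covers serious or unexpected events without a relatedness condition. That provision triggers a review, however. It is not a way of collecting the common digestive and intolerance complaints that section 2.8 itself names.

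Third, the article does not list a between-arm harm comparison as an objective. Its low-risk remark concerns dietary changes in general, and its guideline remark concerns mental health effects. That is fair, and it limits the point to any such comparison that is later made or read into the data.

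Finally, message templates and adverse-event forms usually sit in a fuller protocol, so their absence here is no fault. The point does not rest on their absence. It rests on a scope that the article does state.

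**Conclusion.** The concern holds in limited form. The stated scope of the fortnightly monitoring makes it likely that non-serious digestive and intolerance complaints will be under-recorded in controls relative to the nut arms, so a comparison of minor harms between arms could be biased against nuts.

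The size cannot be determined from the article. In the illustration with a 20% true rate in every arm, the false-signal probability rises from about 4% to about 31% if controls are captured half as well. At assumed rates of 10% and 30%, the half-capture figures are 11.5% and 51.7%. The near-certain false signal belongs to an extreme that the documents do not establish. All these figures rest on assumed complaint rates, assumed capture fractions, full capture in the nut arms and pooling of the two doses.

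The primary efficacy analysis is not affected. The change is worth making because it is easy before recruitment starts, and unrecorded control complaints cannot be recovered afterwards.

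**What to change.** In section 2.8, replace the relatedness-based scope with a uniform one:

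1. At each fortnightly contact, put the same short, fixed set of questions to all three arms. Ask about any new symptom since the last contact, naming digestive and allergic symptoms, whatever the suspected cause.
2. Record suspected relatedness afterwards, as a separate field.
3. Report events by randomised arm, with control as the comparator.

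The existing rules on stopping the intervention and on medical referral are outside this point and need no change for it.

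The cost is a reworded message template and one extra data field. The small downside is more minor events to log, including in the control arm. In the illustration, equal capture returns the false-signal probability to 3.3% to 4.0% across the three assumed rates.

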### 2.9. Data Collection and Clinical Assessments

Data collection and clinical assessments will be centralized at the MOVIFitness laboratory (UCLM, Cuenca) to ensure the standardization of all operational procedures. The protocol allows for the scheduling of a maximum of 15 participants per weekday, with sessions lasting approximately 3 h. These visits include the collection of venous blood samples following at least 12 h of overnight fasting, physical examinations, and cognitive testing guided by a trained multidisciplinary research team. To ensure data integrity and minimize transcription errors, validated Spanish versions of the instruments will be administered via a touchscreen tablet interface using the secured Qualtrics platform (Qualtrics, Provo, UT, USA), which facilitates both participant confidentiality and logistical portability within the clinical environment.

A food frequency questionnaire will be provided in printed format to allow for scanning. For all study variables, the participants will be informed about the procedure of the tests and instructed by a multidisciplinary research team.

### 2.10. Study Variables

Table 1 presents a summary description of the variables collected and the instruments used.

The established cutoff points for specific variables within this protocol are not rigidly fixed and possess inherent flexibility. These thresholds are subject to potential future modifications in subsequent research endeavors. Such adjustments will be driven primarily by the specific aims and hypotheses proposed by the research team, ensuring optimal alignment with evolving research objectives.

The same data collection protocol (including all study variables) applied at baseline (visit 1) will be applied at the 3-month follow-up (intermediate visit 2) and the 6-month post-intervention assessment (final intervention visit 3). Upon completion of the intervention, participants will be instructed to follow their dietary and lifestyle habits without specific restrictions. They will be invited to attend a final data collection session at 12 months (visit 4), i.e., 6 months after visit 3. Once the results of each assessment are available, participants will receive recommendations to consult their primary care physician or emergency services, if necessary.

#### 2.10.1. Primary Mental Health Outcome Measures

Depressive symptoms: The assessment of depressive symptomatology will be conducted using the Beck Depression Inventory–II (BDI-II) [63], a widely validated 21-item self-report measure designed to evaluate the severity of depressive symptoms over the preceding two weeks. Each item offers four response options scored from 0 to 3, with higher scores reflecting greater depressive severity. The BDI-II is considered the gold-standard screening instrument for individuals aged 13 years and older [64]. The Spanish version of the BDI-II has previously been validated [64] and has demonstrated good internal consistency (Cronbach’s α = 0.89) and strong construct and criterion validity across university students [65]. The total scores range from 0–63 and are derived from the sum of all 21 items. Conventional cutoffs classify symptom severity as minimal or absent (0–13), mild (14–19), moderate (20–28), or severe (29–63).

Anxiety symptoms: Anxiety symptoms will be assessed using the Generalized Anxiety Disorder 7-item scale (GAD-7) [66], a validated self-report instrument developed to screen for and quantify the severity of generalized anxiety symptoms over the preceding two weeks. The participants rated each item on a four-point scale ranging from 0 (“not at all”) to 3 (“nearly every day”), yielding a total score between 0 and 21. Higher scores indicate greater anxiety symptomatology, with established cutoffs categorizing symptom severity as mild (5–9), moderate (10–14), or severe (15–21) proposed [66]. The Spanish version of the GAD-7 [67] shows excellent reliability values (Cronbach’s α = 0.94) and good accuracy in identifying cases of GAD (sensitivity and specificity > 0.80) [66,67], including among university students (Cronbach’s α = 0.90) [68].

Stress: Perceived stress levels will be measured using the 10-item Perceived Stress Scale (PSS-10) [69,70], a widely validated self-report instrument designed to assess the degree to which individuals appraise situations in their lives as stressful over the previous month. Each item is rated on a 5-point Likert scale ranging from 0 (“never”) to 4 (“very often”), resulting in a total score between 0 and 40, where higher scores indicate greater perceived stress. Validation studies have reported satisfactory internal consistency for the Spanish version of the PSS-10 (α = 0.82) [70]. Since no validated cutoff scores exist for the PSS-10, it will be analyzed as a continuous variable, and the study sample will be classified into tertiles for comparative analysis.

Cognition: Cognitive performance will be evaluated at the 4 assessments with the National Institutes of Health (NIH) Toolbox Cognition Battery (Chicago, IL, USA), which is administered on an iPad by trained personnel. This widely used computer-based method has been normed for children and adults aged 3–85 years [71]. Specifically, the Fluid Cognition Composite Score will be measured [71], as it is more sensitive to changes resulting from lifestyle interventions than is crystallized cognition [72]. This composite score assesses executive function, processing speed, working memory, episodic memory, and attention through five individual test instruments (~30 min), including the Flanker Inhibitory Control and Attention Test (Flanker) (inhibitory control and attention), the Dimensional Change Card Sort (DCCS) (cognitive flexibility), the Picture Sequence Memory Test (PSMT) (episodic memory), the List Sorting Working Memory Test (LSWM) (working memory), and the Pattern Comparison Processing Speed Test (PCPST) (processing speed). Equivalent alternate forms of the subtests will be administered during follow-up assessments to minimize practice effects. Age-standardized scores for each evaluation and the fluid composite score will be used as the main outcomes of cognitive function. The age-adjusted fluid cognition composite score of the Spanish NIH Toolbox has shown good reliability (ω = 0.78) [73] and moderate to strong convergent validity with established neuropsychological measures [73].

